### Safety/dose-limiting toxicity

2.9

Toxicity will be graded according to the National Cancer Institute CTCAE (v5.0) and the CRS grading system by Lee et al. (36). All AEs and SAEs will be documented and reported according to good clinical practice guidelines. Furthermore, we will report on AESIs, which include occurrence of CRS, infusion-related reactions upon study drug administration and drug induced liver injury (DILI). These AESIs will be monitored closely and included in patient safety narrative reports to the data safety monitoring board (DSMB).

DLT is defined as any AE grade ≥3 that the investigator considers to be at least possibly related to study treatment and occurring within the DLT safety period (from first study drug treatment to day 21 or 28, respectively, if an additional intermittent priming dose is given) with few exceptions. Notably, grade ≥3 CRS lasting less than 48 h, grade ≥3 nausea, vomiting or diarrhea in patients who have not received optimal antiemetic or antidiarrheic treatment, as well as isolated ≥3 laboratory abnormalities resolving within 7 days and without clinical sequelae are not considered a DLT. Likewise, liver toxicity caused by obstruction, metastasis, or infection; grade ≥3 transaminitis or direct hyperbilirubinemia for <4 days; grade 3 fatigue for ≤5 days; grade 3 infusion reaction resolving within 8 h; nor grade 3 but adjustable (i.e., not refractory) arterial hypertension are not considered a DLT.

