### Study approach

2.3

This FIH study will consist of two parts: a dose-escalation part comprising an accelerated titration phase in which the dose level (DL) is fixed for the individual patient but may increase with each patient by up to 100%, depending on safety considerations judged by an SRC. In case of CC-3–induced adverse events (AEs) ≥grade 2 according to Common Terminology Criteria for Adverse Events (CTCAE) version 5.0, dose-limiting toxicity, reaching a DL of ≥800 µg or SRC decision, this accelerated titration phase will be switched to a standard 3 + 3 dose–escalation design. At this stage, dosing will be split in a priming dose (last DL of the accelerated titration part with no AE ≥2 and no DLT) and a target dose (DL at which the stopping criterion was observed that terminated the accelerated titration part). Three patients will be enrolled in this first cohort. If one of these three develops DLT, then three additional patients will be recruited into the cohort. If two patients develop DLT, then the dose is de-escalated to the last DL considered as safe. If no patient of this cohort experiences DLT, then the next DL will be determined by the SRC and applied to a second cohort. This will again consist of three patients and follow the same DLT considerations as the previous cohort. This will be repeated until MTD is determined, with MTD defined as no more than one of the six patients experiencing DLT. Once the MTD is determined, dosing will be fixed at this level. Then, further patients will be recruited until 20 patients altogether have received CC-3 at the MTD. This dose-expansion part will serve to confirm the RP2D and to detect first signs of clinical efficacy (see also **Figures 1**, **2**).

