**Figure 2 f2:**
[figure not shown]
Dose-escalation part. **(A)** Dosing. First patient (Pat 1) receives 50 µg weekly over 16 weeks. During 3 weeks after first application, dose-limiting toxicity (DLT) will be evaluated and the dose level (DL) for the next patient (Pat 2) will be determined by safety review committee (SRC). Repetition of SRC-guided accelerated dose escalation with following patients until occurrence of DLT, AEs ≥2, or decision of SRC, in patient X (Pat X). Switch to 3 + 3 design with last DL before reaching a criterion (Pat X-1) being used as a priming dose (green frame) for the first application, followed by the DL at which the stopping criterion was observed (Pat X) in subsequent applications. When last patient of each cohort has been observed for 21 days after application of target dose, DLT will be evaluated and the dose level for next cohort of at least three patients is determined by SRC. * up to two additional subjects may be enrolled at each DL; ** up to six additional subjects may be enrolled at each DL; *** SRC may decide to add one additional priming dose, so that target dose is reached at week 3 and DLT evaluation period thus prolonged until end of week 4 (dashed lines). **(B)** Flowchart. If no DLT, AEs grade ≥2, or respective decision of SRC occurs, dose levels may be incremented by up to 100% during accelerated dose titration, enabling a rapid increase up to the maximum target dose after a potential minimum of eight patients. After switching to 3 + 3 design, the number of patients per cohort depends on occurrence of DLT, until maximum tolerated dose (MTD) is reached.

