#### Dose-escalation part

2.7.1

Initially, dose escalation will be conducted using an accelerated titration design with single-patient cohorts for each DL. Up to two additional subjects may be enrolled at each DL in case more PK, pharmacodynamic (PDK), or safety data are deemed necessary by the SRC. A staggered enrollment design is used for each DL, with a minimum observation period of 72 h between two consecutive subjects’ first doses with the same DL. This is considered sufficient to identify CRS as most critical toxicity. Every patient receives a fixed dose, starting with 50 µg in the first cohort. Subsequent doses are determined by the SRC based on PK, PDK, and safety data obtained with the last DL over an observation period of 21 days, during which DLT evaluation is conducted. This accelerated phase will be replaced by a standard 3 + 3 design in case of

any AE grade ≥2 (except AEs unequivocally due to underlying disease or an extraneous cause);occurrence of DLT;DL ≥800 µg; anddecision of SRC based on PK, PDK, and safety data.

In the standard titration phase of the dose-escalation part, the last DL safely applied prior to termination of the accelerated phase is used as priming dose upon first application, followed by the DL at which the stopping criterion was observed in week two and thereafter. Based on PK, PDK, and safety data, the SRC may decide to introduce an additional intermittent priming dose at week 2, in which case the target dose will be applied at week 3. At least three patients are treated per cohort, following a rule-based 3 + 3 design. Up to a maximum of nine patients per cohort may be enrolled if more PK, PDK, or safety data are deemed necessary by the SRC. After completion of the first cohort’s DLT evaluation period (21 days after application of the target dose to the last patient), the DL for the next cohort will be determined by the SRC. This will be done considering all AEs and DLTs as well as PK, PDK, and safety data. The DL can be increased up to 100% of the previous dose. The priming dose applied in the first cohort will further be given at week 1 of every consecutive cohort, followed by the target dose at week 2 or 3, depending on whether the SRC deemed an intermittent priming dose necessary at week 2 (**Figure 2A**).

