### Endpoints of the study

2.8

The primary endpoints of the dose-escalation part are incidence and severity of AEs, including AESIs, serious AEs (SAEs) and suspected unexpected serious adverse reaction (SUSARs) [CTCAE v5.0 and for CRS modified criteria by Lee et al. (36)], from first application of CC-3 at week 1 until week 4 or, in case of early termination, last assessment. The primary endpoints of the dose-escalation and dose-expansion parts are the best objective response, defined as stable disease (SD), partial remission (PR), or complete remission (CR) until end of study (EOS) compared to baseline based on routine imaging according to RECIST 1.1.

Secondary endpoints include general long-term safety, product-specific safety aspects, clinical efficacy endpoints, and pharmacokinetics:

• Safety (general): incidence and severity of AEs including AEs of special interest (AESIs), SAEs, and SUSARs according to CTCAE v5.0 from first application of CC-3 until EOS visit or, in case of early termination, last assessment• Efficacy:  ○ Objective tumor response assessed by RECIST 1.1 on routine imaging at week 8, week 16, and at EOS visit;  ○ Disease control rate (CR, PR, and SD) at each visit until end of the clinical trial.• Survival:  ○ OS defined as the time from first administration of CC-3 to time of death from any cause. Patients without the event are censored on the last date of follow-up;  ○ Progression-free survival defined as the time from first administration of CC-3 to progression of disease or death from any cause, whichever occurs first. Patients without the event are censored on the last date of follow-up.• Pharmacokinetics: CC-3 serum concentrations assessed at week 1, week 2, and, in case of second priming dose, at week 3• Quality of life: overall quality-of-life scores (EORTC QLQ C-30) at screening visit, week 5, week 9, week 13, end of treatment (EOT) visit, follow-up (FU) visit, and EOS visit.

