### SRC and DSMB

2.10

Trial conduct will be overseen by an SRC composed of at least three members, including the coordinating investigator and a representative of the sponsor. It receives reports routinely 21 days after first dose of CC-3 of each single patient in the accelerated titration phase and as soon as three patients per cohort have completed the DLT evaluation period of 21 days after target dose application in the standard titration phase. The SRC assesses all available data on safety, PK, and PDK and determines the dose for the next cohort.

The DSMB is composed of three independent experts assessing study progress and safety data. It receives reports routinely after the end of the accelerated titration phase, after the end of the standard titration phase, upon request by the SRC, or in case of occurrence of DLT.

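### In the 3+3 phase the DLT window is stated in two incompatible ways: to day 21 or 28 from first dose, or 21 days after the target dose (about day 28 or 35)

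*Protocol article*

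**What the plan says.** All references are to the protocol article. In the standard titration phase a patient first receives a priming dose, and the target dose follows in week 2. The SRC may add a second priming dose in week 2, which moves the target dose to week 3 (section 2.7.1).

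The shorter window appears in two places:
- Section 2.9, which defines a DLT, limits the period to the time "from first study drug treatment to day 21 or 28, respectively, if an additional intermittent priming dose is given".
- The Figure 2 legend, in its note on a second priming dose, says the SRC may add that dose "so that target dose is reached at week 3 and DLT evaluation period thus prolonged until end of week 4".

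The longer window appears in three places:
- Section 2.7.1 describes the first cohort's DLT evaluation period as "21 days after application of the target dose to the last patient".
- Section 2.10 has the SRC receive its report once three patients per cohort have "completed the DLT evaluation period of 21 days after target dose application in the standard titration phase".
- The Figure 2 legend also says: "When last patient of each cohort has been observed for 21 days after application of target dose, DLT will be evaluated".

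The DLT count drives the design. Section 2.3 states "If one of these three develops DLT, then three additional patients will be recruited into the cohort", de-escalates when two patients have a DLT, and closes the escalation "with MTD defined as no more than one of the six patients experiencing DLT".

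**The concern.** The DLT count is the decision variable of a 3+3 design, and the number of days over which events count is part of its definition. Here the section that defines a DLT and the sections that say when DLTs are evaluated give different end points for the same patients. The Figure 2 legend contains both versions.

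An event in the disputed week is therefore classified according to which section the reader follows. That classification decides whether a cohort is expanded or the dose is lowered, and which dose level becomes the MTD. The MTD is then the dose carried into the expansion part, where 20 patients in all are to receive it.

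**Working it through.** **Inputs.** Infusions are weekly (section 2.7). The first target dose is in week 2 with one priming dose and in week 3 with two (section 2.7.1). The stated ends are day 21 and day 28 from first dose (section 2.9) and 21 days after the target dose (sections 2.7.1 and 2.10, Figure 2 legend). The article does not say whether the first infusion is day 0 or day 1, so both are tried.

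**Formula.** Day of first target dose = 7 × (week − 1) + day number of the first infusion. Window end = that day + 21.

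| Schedule | First infusion | First target dose | Target dose + 21 days | End in section 2.9 | Difference | Days after target dose at the section 2.9 end |
|---|---|---|---|---|---|---|
| One priming dose | day 0 | 7 | 28 | 21 | 7 | 14 |
| One priming dose | day 1 | 8 | 29 | 21 | 8 | 13 |
| Two priming doses | day 0 | 14 | 35 | 28 | 7 | 14 |
| Two priming doses | day 1 | 15 | 36 | 28 | 8 | 13 |

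The figures in section 2.9 are not reproduced under either numbering. With the first infusion as day 1 and both end days counted inclusively, the shorter window holds 14 days of target dosing (days 8–21 or 15–28) and the longer one 21 days (days 8–28 or 15–35). The difference is 21 − 14 = 7 days. On that numbering, two target infusions fall in the shorter window (days 8 and 15, or 15 and 22) and three in the longer one. If the first infusion is day 0, the third target infusion falls on the last day of the shorter window.

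**Can the texts be reconciled?**
- *Day 21 for the accelerated phase and day 28 for the 3+3 phase with one priming dose.* This would match 21 days after a week-2 target dose. However, section 2.9 ties day 28 to the additional priming dose, which section 2.7.1 defines as the optional second one, and the Figure 2 note ties the end of week 4 to a week-3 target dose. The schedule with two priming doses, which needs about day 35, would still not be covered.
- *Two different periods, one for counting and one for waiting.* Section 2.9 does speak of a safety period, and sections 2.7.1 and 2.10 of an evaluation period. But the Figure 2 note applies the evaluation term to the shorter window. Whatever the name, section 2.9 fixes which events are DLTs, so an evaluation period running a week longer would contain a week in which no event could count.

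The two rules agree only in the accelerated phase, where there is no priming dose and 21 days run from the first dose.

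**Effect on a decision.** Take one priming dose and a cohort of three. Patient A has a DLT by day 21. Patient B, a different patient, has a related, non-exempt grade 3 event on day 24.
- Section 2.9: 1 of 3, so three more patients are enrolled.
- Sections 2.7.1 and 2.10: 2 of 3, so the dose is de-escalated.

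The same two events in a cohort of six give 1 of 6, which meets the MTD definition, or 2 of 6, which does not.

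**The case against.** The strongest reply is that little depends on this in practice. Three statements make the SRC wait 21 days after the target dose. Section 2.7.1 has it choose the next dose on all adverse events together with pharmacokinetic, pharmacodynamic and safety data, and it may enlarge a cohort to nine. A grade 3 event on day 24 would be seen and weighed before anyone is escalated. This stands. A reader might infer from the shorter window that late toxicity goes unobserved or that escalation runs ahead of the data, and the documents do not support that. What remains is that the expansion, de-escalation and MTD rules are written on DLT counts, and the count is ambiguous.

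The reply may add that the second-priming note is the only place where the shorter window is called the evaluation period, that it covers only the optional schedule, and that it refers to a figure not shown. That is fair as to terminology. It does not touch the conflict between the DLT definition in section 2.9 and sections 2.7.1 and 2.10.

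A reader might also enlist the primary adverse event endpoint in section 2.8, which runs "from first application of CC-3 at week 1 until week 4 or, in case of early termination, last assessment". It favours neither side. If week 4 ends on day 28, it coincides with the longer window under one priming dose and with the shorter one under two. It is a reporting window that also applies to accelerated-phase patients, and it does not define a DLT. Nothing requires it to contain the DLT window, and the secondary safety endpoint follows adverse events to the end-of-study visit.

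**Conclusion.** The contradiction is real and lies within the current text. For the standard 3+3 phase the DLT window ends either at day 21 or 28 from first dose, or about 7 days later. No reading of the article makes these agree, and the article does not settle which was meant.

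The size that can be stated firmly is the gap: about one week per patient in either schedule, which is one third of the 21 days that sections 2.7.1 and 2.10 allow after the target dose (7/21). The effect on the chance that a dose passes, or on the MTD itself, cannot be fixed. It depends on the DLT risk and on when DLTs occur, and the documents give neither. It may be close to nil if DLTs come early. Section 2.7.1 regards 72 hours as enough to identify cytokine release syndrome, though section 2.9 exempts grade 3 or higher episodes shorter than 48 hours, so the timing of that syndrome need not describe the timing of DLTs. A claim that the MTD will be set too high by a given amount would go beyond the documents.

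The calendar result assumes weekly dosing on schedule, and the one-day uncertainty in day numbering does not alter it. The text should be corrected because the ambiguity sits in the definition that drives every 3+3 step.

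**What to change.** In section 2.9 and in the Figure 2 legend, including its note on a second priming dose, define the standard-phase DLT window as first CC-3 dose through 21 days after the first target dose. Give the resulting end as about day 28 with one priming dose and day 35 with two, and say how days are numbered. State that this window is used for all 3+3 and MTD counts. Keep day 21 from first dose for the accelerated phase. The primary adverse event endpoint in section 2.8 needs no change.

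The longer window is the sensible choice because it matches the wait that sections 2.7.1 and 2.10 already require. If that wait is kept, the cost is wording only, with no added calendar time. One consequence should be accepted openly: compared with the shorter window, the longer one can only add DLTs, so the resulting MTD may be lower.

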Efficacy of currently available bsAbs and CAR T cells is additionally hampered by side effects due to unspecific activation of the T cells, resulting in a potentially lethal cytokine release syndrome (CRS) (23, 24). This is due to the employed target antigens frequently being not exclusively expressed not only on malignant but also on healthy cells. Thereby, not only are the patients endangered, but also the application of truly effective doses prevented. Recently, we have developed the PSMAxCD3 bsAb CC-1 in an optimized immunoglobulin G (IgG)–based bsAb format (IgGsc) that displays a prolonged half-life and strictly target-restricted activity with accordingly reduced off-target toxicity (25). CC-1 is currently clinically evaluated in patients with prostate cancer (NCT04104607 and NCT05646550) (26). Recently, the target antigen CD276 (also known as B7-H3) has received large interest due to its broad but rather tumor-restricted expression on cancer cells and neovasculature/microenvironment, including CRC (27, 28). Although this molecule has been shown to have costimulatory effects on T cells in mouse models, it is, meanwhile, considered mainly as inhibitor of human T-cell function, e.g., by suppressing interleukin-2 (IL-2) (27). Preparative work for this clinical trial revealed relevant CD276 expression in all investigated metastatic CRC samples. This prompted us to generate a CD276xCD3 bsAb in our IgGsc format CC-3 that, like CC-1, exhibits an optimal half-life but lacks unspecific T-cell activation while having potent antitumor activity (29) intended for treatment of CRC. Presently widely used targets for CAR T cells and bsAbs in preclinical and early clinical stages of development for CRC treatment are epidermal growth factor receptor (EGFR) and carcinoembryonic antigen (CEA) (19, 30, 31). Compared with these and other immunotherapeutics currently in development, targeting CD276 with CC-3 is expected to

cause fewer side effects due to its optimized bsAb format and choice of TAA, which will allow for the application of effective bsAb doses and accordingly increased efficacy;enable “dual targeting” of tumor cells and neovasculature, which will improve the immune effector cells’ access to CRC tumors, facilitating therapeutic success;be a readily available “off the shelf drug,” eliminating the preparatory work required for CAR T-cell production delaying treatment; andallow for convenient dosing schedules according to its prolonged half-life (32).

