For instance, example 1 (a conservative example) as shown in **Table 1**—(i) a 50% dose increase between cohorts, (ii) one patient treated per cohort in the accelerated titration phase (three cohorts in total), (iii) six patients per cohort in the standard titration phase (10 cohorts in total), (iv) a starting dose of 50 µg, and (v) a maximum tested dose of 4,000 µg—requires a total number of 63 patients in the dose-escalation part.

**Table 1 T1:** Example 1 (a conservative example) of target dose levels in the dose-escalation part.

Level	D1	D2	D3	D3	D4	D5	D6	D7	D8	D9	D10	D11	D12
Cohort	1	2	3	4	5	6	7	8	9	10	11	12	13
Dose (µg)	50	75	113	113*	169	253	380	570	854	1,281	1,922	2,883	4,000
Assumed number of patients per cohort	1	1	1	6	6	6	6	6	6	6	6	6	6
Phase	A	A	A	S	S	S	S	S	S	S	S	S	S

*Standard titration phase is started with new cohorts of initially up to three patients. Treatment schedule is altered to introduce a priming dose on T1V1, leading to application of target dose on T2V1 and consecutive treatment das; A, accelerated titration phase (light gray); S, standard titration phase (dark gray).

Example 2 (a progressive example) as shown in **Table 2**—(i) a 100% dose increase between cohorts, (ii) one patient treated per cohort in the accelerated titration phase (four cohorts in total), (iii) upon a DL of ≥ 800 µg of three additional cohorts with three patients each, (iv) six patients treated in the last cohort of the standard titration phase, (v) a starting dose of 50 µg, and (vi) a maximum tested dose of 4000 µg—requires a total number of 19 patients in the dose-escalation part.

**Table 2 T2:** Example 2 (a progressive example) of target dose levels in the dose-escalation part.

Level	D1	D2	D3	D4	D5	D6	D7	D8
Cohort	1	2	3	4	5	6	7	8
Dose (µg)	50	100	200	400	800	1,600	3,200	4,000
Assumed number of patients per cohort	1	1	1	1	3	3	3	6
Phase	A	A	A	A	S	S	S	S

A, accelerated titration phase (light gray); S, standard titration phase (dark gray).

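### The DLT exemption for CRS lasting under 48 h has no upper grade, so in the 3+3 phase a short grade 4 or higher CRS does not count in the dose rules, the MTD criterion or the DSMB's DLT trigger

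*Protocol article*

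**What the plan says.** Section 2.9 (Safety/dose-limiting toxicity) defines a DLT as an adverse event of grade 3 or worse, judged at least possibly related to treatment, within the DLT period. It then lists exceptions, among them "Notably, grade ≥3 CRS lasting less than 48 h". No ceiling is attached to that grade. Later in the paragraph some exceptions do stop at grade 3, for example "grade 3 infusion reaction resolving within 8 h"; fatigue and controllable hypertension are treated the same way. Others are open-ended like CRS: gastrointestinal events without optimal supportive treatment, isolated laboratory abnormalities, and short-lived transaminase or direct bilirubin elevations.

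Three mechanisms use the DLT definition:

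- **3+3 steps** (sections 2.3 and 2.7.1): "If one of these three develops DLT, then three additional patients will be recruited into the cohort"; two DLTs lead to de-escalation.
- **MTD** (sections 2.3 and 2.7.1): at most one of six patients with a DLT.
- **DSMB reporting** (section 2.10): routine reports after each titration phase, plus a report at the SRC's request or when a DLT occurs.

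Section 2.7.1 calls CRS the critical toxicity when it justifies the 72 h stagger between patients: "This is considered sufficient to identify CRS as most critical toxicity". The Introduction describes CRS from this class of agents as potentially lethal.

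On dose selection after a 3+3 cohort, section 2.7.1 says: "This will be done considering all AEs and DLTs as well as PK, PDK, and safety data".

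**The concern.** A 3+3 design protects patients through its count. If an event is not a DLT, the rule does not see it. Here the exempted event is the toxicity that the article itself singles out, and the exemption depends on duration alone. A CRS that was life-threatening for a day and a half would leave the cohort's DLT count at zero.

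Three things are at stake: whether the next cohort's dose is held back by rule or only by judgement, whether the dose called the MTD has been screened for severe short CRS, and whether such an event by itself brings the DSMB in before its next routine report.

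**Working it through.** **Step 1. Read the definition against neighbouring cases.** All events are taken as at least possibly related and within the DLT period.

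| Event | Exempt under section 2.9? | DLT? |
|---|---|---|
| Grade 3 infusion reaction, resolved within 8 h | yes | no |
| Grade 4 infusion reaction, resolved within 8 h | no, exemption stops at grade 3 | yes |
| Grade 3 CRS, 47 h | yes | no |
| Grade 4 CRS, 47 h | yes, no upper grade | no |

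No other part of the article brings grade 4 or higher CRS back in as a DLT.

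**Step 2. Follow the event through the rules.** Suppose two of the first three patients in a 3+3 cohort have a grade 4 CRS of 47 h and no other DLT. The DLT count is 0 of 3. By rule the cohort is not expanded, the dose is not de-escalated, and the SRC may set a next dose up to 100% higher. The events do not count towards the MTD limit and do not trigger a DSMB report.

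**Step 3. Where the gap applies.** It is confined to the 3+3 phase. In accelerated titration, any AE of grade 2 or higher that is not clearly due to disease or an outside cause ends the single-patient cohorts (section 2.7.1), and a routine DSMB report follows the end of that phase (section 2.10).

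**Step 4. Illustration of size.** The article gives no rate for short grade 4 CRS or for other DLTs and no operating characteristics, so there is no printed figure to reproduce. The rates below are assumptions, and SRC judgement is left out. Let p be the per-patient probability of an event that counts.

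- Passing the 3+3 count (0 of 3, or 1 of 3 followed by 0 of 3): f(p) = (1−p)³ + 3p(1−p)⁵
- Meeting the MTD criterion: P(X ≤ 1) with X ~ Bin(6, p), which is (1−p)⁶ + 6p(1−p)⁵
- At least one DLT in the first three patients (DSMB trigger): 1 − (1−p)³

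With other DLTs at 10%, p stays at 0.10 as written, whatever the CRS rate. If short grade 4 CRS counted, p would be 0.10 plus the rate of such events in patients without another DLT.

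| Added short grade 4 CRS | p | Pass 3+3 | At most 1 of 6 | DLT in first 3 |
|---|---|---|---|---|
| any rate, as written | 0.10 | 0.906 | 0.886 | 0.271 |
| 5%, counted | 0.15 | 0.814 | 0.776 | 0.386 |
| 10%, counted | 0.20 | 0.709 | 0.655 | 0.488 |
| 20%, counted | 0.30 | 0.494 | 0.420 | 0.657 |
| 30%, counted | 0.40 | 0.309 | 0.233 | 0.784 |

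Example: f(0.10) = 0.729 + 0.3 × 0.59049 = 0.906, and f(0.20) = 0.512 + 0.6 × 0.32768 = 0.709.

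**Step 5. Sensitivity.** For the same added rates, with other DLTs at 5% the pass probability is 0.973 as written against 0.906 to 0.396. At 15% it is 0.814 against 0.709 to 0.234. If the two event types are taken as independent instead of additive, a 10% CRS rate with 10% other DLTs gives p = 1 − 0.9 × 0.9 = 0.19 and a pass probability of 0.730 instead of 0.709. The direction does not change.

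**The case against.** **The SRC is the real brake.** It considers all adverse events and not only DLTs. It need not escalate, may enlarge a cohort to nine patients, may add a second priming dose and may ask for a DSMB report. CRS is an adverse event of special interest whose cases are "included in patient safety narrative reports to the data safety monitoring board (DSMB"), and a substantial amendment precedes expansion (section 2.7.2). This stands, and a reader should not infer that a short grade 4 CRS would go unseen. But these safeguards are discretionary or come later, and none changes the DLT count that defines the MTD.

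**CRS is not treated uniquely.** A reader might infer that the rule is loosest for the event that matters most. Section 2.9 does not support that. Several other exemptions are also open above grade 3, and the 48 h window is shorter than those for transaminase elevation (under 4 days) and laboratory abnormalities (7 days). Liver toxicity from obstruction, metastasis or infection is exempt with no grade or duration limit.

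**Patients treated between routine DSMB reports.** Table 1 implies 10 × 6 = 60 standard-phase patients, and it is tempting to say that 60 could be treated without the DSMB being alerted. That does not follow. Under the 3+3 rule a cohort usually grows from three to six because a DLT occurred, and each DLT triggers a report; the other route is an SRC request for more data. Table 2, with "three additional cohorts with three patients each, (iv) six patients treated in the last cohort of the standard titration phase", gives 3 × 3 + 6 = 15, which is also only a planning example.

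**The exemption may be deliberate, and the full protocol is not shown.** Excusing brief CRS is a legitimate trade-off, and the article introduces its list as a selection of exceptions. The full protocol may cap the grade. The published definition nevertheless states a threshold explicitly, and that threshold has no cap.

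**Conclusion.** The point holds as a defect in the printed DLT definition that is cheap to correct. In the 3+3 phase, a related CRS of grade 4 or higher lasting under 48 h is outside the 3+3 steps, the MTD criterion and the DSMB's DLT trigger. This follows from the text and needs no assumption about rates.

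The probabilities are an illustration only. They rest on assumed event rates and on the DLT count acting alone, without the SRC. They show that the printed rule cannot respond to short grade 4 CRS at any rate. A reader might infer from them that the MTD of this trial will be materially too high. The documents do not support that, because they give no rate for such events, the design uses priming doses, and the SRC sets each dose.

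Confidence is medium, because the full protocol might already contain the cap.

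**What to change.** In section 2.9, limit the exemption to grade 3 CRS that resolves to grade 2 or lower within 48 h, and state that any CRS of grade 4 or higher at least possibly related to CC-3 is a DLT. If the full protocol already says this, the published definition should be brought into line with it.

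The cost is one line of wording, with no change to the visit schedule or planned sample size. The downside is that escalation may be slower or the MTD lower if such events occur.
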